### Participants

Following recommendations from Lakens [49] and Aberson [50], powering for interaction effects is considered essential in behavioral intervention trials where the primary interest lies in differential changes across conditions. Accordingly, the sample size calculation is based on the statistical power required to detect a time × group interaction effect, estimated using the “ANOVA: Repeated measures, within–between interaction” model in G*Power 3.1. Assuming a medium effect size f = 0.25 (Cohen’s standard), α = 0.05, power = 0.95, three groups, two measurement time points, and an intra-class correlation (ICC) of 0.5, the estimated result shows that the study requires at least 66 participants (22 per group) to ensure sufficient power for detecting the interaction effect. Considering a potential dropout rate of 15% [51], a total of 76 golfers will be recruited. If practical resource constraints result in a slightly smaller sample size, the study will report effect sizes and Bayes factors to supplement the interpretation of statistical significance and cautiously delimit the generalizability of conclusions to ensure the scientific rigor and interpretability of the results.

Participants in this study will be selected from the National Colleges and Universities Golf Championship (NCUGC) in China. The research team will collaborate with the head coaches of the participating teams to determine the universities willing to participate. Subsequently, the head coaches and team physicians will conduct an initial screening of players based on the inclusion criteria set for this study (Table 1). The research team will then verify the eligibility of the selected participants before the experiment begins.

**Table 1 pone.0337905.t001:** Participant selection criteria.

Inclusion criteria	Exclusion criteria
Aged 18–24 years old	Color blindness
Golfers of the NCUGC	Hearing loss
Least 3 years of specialized golf training	Insomnia
Least 5 trainings per week	Experiencing any physical injury
	Experiencing mental health issues
	Receiving any medication

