### Statistical analysis

All statistical tests will be conducted at a significance level of α = 0.05, with effect sizes measured using partial eta squared (η²p). The statistical power is set at 0.80, and all analyses will be performed using IBM SPSS Statistics 27.0. This study will adopt a 2 (Time: pre-test vs. post-test) × 3 (Group: mental fatigue–music intervention group, mental fatigue–non-music group, control group) mixed-design repeated measures ANOVA to examine the effects of mental fatigue and music intervention on golf-specific skill performance. The core hypothesis of the study is the time × group interaction effect, which aims to determine the performance differences across groups before and after the intervention, thereby verifying the potential value of music intervention under mental fatigue. Time main effects and group main effects will serve as secondary analysis objectives.

Prior to the main analysis, a one-way ANOVA will be conducted to compare baseline skill performance across the three groups to assess initial group equivalence and ensure the validity of subsequent comparisons. In the main effects analysis, mixed-design repeated measures ANOVA will be used to test the time main effect (whether overall skill performance changes over time), group main effect (whether there are overall differences among the three groups), and the time × group interaction effect (whether skill performance changes differ among the groups). If the assumption of sphericity is violated, the Greenhouse-Geisser or Huynh-Feldt correction will be applied to adjust the degrees of freedom. If the interaction effect is significant, simple effects analysis will be conducted to clarify the performance trends before and after the intervention within each group and to compare differences between groups at each time point.

To control the accumulation of Type I error due to multiple comparisons, all post hoc group comparisons will apply Bonferroni correction. If the study involves multiple primary outcomes or multiple independent hypothesis tests, the Holm-Bonferroni method will be further applied to control the family-wise error rate. In addition, the study will predefine a single primary outcome—ball-shooting accuracy score—while other technical indicators such as shot quality and reaction time will be treated as exploratory outcomes, serving to support and interpret the results but not as primary hypothesis testing targets.

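### The 0.95 power belongs to the three-group interaction; the music comparison needed after it has no stated power and carries a Bonferroni correction that the interaction gate makes unnecessary

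*Protocol article*

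**What the plan says.** Under Participants, "the sample size calculation is based on the statistical power required to detect a time × group interaction effect". The inputs are "Assuming a medium effect size f = 0.25" together with "α = 0.05, power = 0.95, three groups, two measurement time points" and "an intra-class correlation (ICC) of 0.5". The section concludes that "the estimated result shows that the study requires at least 66 participants (22 per group) to ensure sufficient power for detecting the interaction effect".

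Statistical analysis names the interaction as the core hypothesis and presents it as the way to verify the potential value of music under mental fatigue. It then sets the follow-up: "If the interaction effect is significant, simple effects analysis will be conducted", covering change within each group and differences between groups at each time point. For multiplicity, "all post hoc group comparisons will apply Bonferroni correction". The same section also gives a power of 0.80, without saying which test that refers to.

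The Introduction states the aim: to find out whether music offsets the harm that mental fatigue does to skill performance.

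**The concern.** The aim is answered by one contrast, MF-Mu against MF-nMu. The interaction test has two degrees of freedom and responds to any difference in change among the three groups, including both fatigue arms falling equally below control. Its power therefore does not carry over to the music question, and its significance alone does not verify a music effect.

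To reach a statement about music, the written route must pass the interaction at 0.05 and then a Bonferroni-corrected pairwise comparison. No power is given for that sequence. Two things are at stake. A non-significant music comparison could be read as strong negative evidence because the trial was sized at 0.95. And some power is given up to a correction that, with three groups and a matching follow-up, controls no error the gate has not already controlled.

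**Working it through.** **Inputs.** From Participants: f = 0.25, α = 0.05, three groups, two time points, correlation ρ = 0.5, N = 66 (22 per group). From Statistical analysis: simple effects only after a significant interaction, groups compared at each time point, Bonferroni for the group comparisons. Reading the correction as covering three pairs gives 0.05/3 = 0.0167. That count is my reading of three groups.

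**1. The plan's own figure.** λ = f² × N × m/(1 − ρ) = 0.0625 × 66 × 2/0.5 = 16.5, with 2 and 63 degrees of freedom. Noncentral F power is 0.953. The smallest multiple of three that reaches 0.95 is 66, so the figure reproduces. For 0.80, N = 42 would suffice.

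**2. From f to group means.** In units of the SD of a single score, the variance of change is 2(1 − ρ) = 1. The squared deviations of the three mean changes therefore sum to 16.5/22 = 0.75. The protocol does not say how that total is shared among the groups, so I assume patterns. With control at 0 and MF-nMu at −L:

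- Music restores all of the loss, means (0, 0, −L): (2/3)L² = 0.75, so L = 1.06 and the music difference is 1.06 SD.
- Three quarters, (0, −0.25L, −L): 0.5417L² = 0.75, so L = 1.18 and the difference is 0.88 SD.
- Half, (0, −0.5L, −L): 0.5L² = 0.75, so L = 1.22 and the difference is 0.61 SD.
- Music above control, with control midway between the fatigue arms: difference 1.22 SD, the largest pairwise difference that f = 0.25 allows.

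**3. Does the interaction speak to music?** With both fatigue arms at −1.06 SD and no music effect, the simulated interaction is still significant in 95% of trials.

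**4. Power for MF-Mu against MF-nMu.** Bivariate normal scores, pooled error with 63 degrees of freedom, 100,000 simulated trials per pattern. Every column requires a significant interaction first.

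| Pattern | Post-test, 0.0167 (as written) | Change, 0.0167 | Change, 0.05 |
|---|---|---|---|
| Full restoration | 0.83 | 0.85 | 0.92 |
| Three quarters | 0.66 | 0.68 | 0.81 |
| Half | 0.33 | 0.34 | 0.51 |
| Above control, control midway | 0.91 | 0.94 | 0.95 |

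As an exact check without the gate, full restoration has noncentrality 1.061/√(2/22) = 3.52, which gives 0.852 at 0.0167 and 0.934 at 0.05.

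Moving from post-test to change adds 1 to 2 points in the first three rows. Dropping the correction adds a further 7, 13 and 17 points.

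**5. Is error still controlled without Bonferroni?** With three groups, if any two pairwise null hypotheses are true, the third is too. The only intersection hypothesis is therefore that all three mean changes are equal, and the interaction F tests exactly that at 0.05. If just one pair is equal, only one false rejection is possible, and it is tested at 0.05. This is a closed test. The argument requires the follow-up to be on change, the quantity that the gate tests. Simulated family-wise error was about 0.051 with no effects, 0.050 when only MF-Mu and CON are equal, and 0.049 to 0.050 when only the fatigue arms are equal.

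**The case against.** The strongest reply is that nothing in the power statement is wrong. Participants ties the 0.95 to the interaction, Statistical analysis names the interaction as the core hypothesis, and the two agree. That stands. A reader might infer that the trial's stated power is false, and the documents do not support this. What remains is narrower: the analysis section treats the interaction as verifying the value of music, which it cannot do alone.

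A reader might also take 0.83 as a ceiling, or take the drop from 0.95 as a fixed amount. Neither follows. At the same f, power is about 0.88 if music overshoots control by a quarter of the loss, about 0.91 with control midway, and about 0.07 if music restores only a quarter. At full restoration, 0.83 also exceeds the 0.80 in the analysis section, so the serious shortfall depends on partial restoration. The protocol gives no ground either for assuming that or for excluding it.

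Bonferroni after an omnibus test is valid and conventional. That stands too: there is no inflated error, only avoidable loss of power. The redundancy holds only once the follow-up is put on change; as written, groups are compared at each time point.

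Finally, the plan promises Bayes factors and Cohen's d, which would temper the over-reading of a null result. They help with interpretation but do not supply the missing power.

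**Conclusion.** The concern holds as a point about interpretation and efficiency. The 0.95 is right for the interaction and does not carry over to the music comparison. Under the written route, illustrative power for music is about 0.83, 0.66 and 0.33 for full, three-quarter and half restoration, and about 0.91 with music above control. The change-based closed test gives about 0.92, 0.81 and 0.51 for the first three.

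These figures rest on 22 analysed per group, ρ = 0.5, f = 0.25, normal scores with equal variances, assumed mean patterns, and one primary outcome tested at 0.05. The Abstract lists several primary outcomes while Statistical analysis names one. If Holm-Bonferroni across outcomes comes into play, power is lower. Even after the change, half restoration leaves power near one half.

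**What to change.** In Statistical analysis:

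- Replace the Bonferroni-corrected between-group simple effects with three pairwise contrasts of pre-to-post change from the same model (MF-Mu against MF-nMu, MF-nMu against CON, MF-Mu against CON).
- Test each at 0.05 only if the three-group interaction is significant, and state that this is a closed test for exactly three groups.

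In Participants and Statistical analysis:

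- Say that a significant interaction alone does not establish a music effect, and that MF-Mu against MF-nMu is the contrast that addresses it.
- Give the power of that contrast under the new rule as an illustrative range for one primary outcome, with the assumed patterns: about 0.92, 0.81 and 0.51 for full, three-quarter and half restoration.
- Reconcile the 0.95 with the 0.80, or say which test each refers to.

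The cost is wording; no participants or measurements are added. Status and timeline says that neither recruitment nor data collection has begun, so the rule can be changed before any data exist. The downsides are that the stated power for the music question will look less favourable than 0.95, and that the pairwise tests then depend on the interaction gate for error control, so they may not be reported as confirmatory when the gate fails.

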All statistical analyses will report effect size indicators. For significant results, partial eta squared (η²p) will be reported as the effect size for ANOVA, and Cohen’s d will be calculated for between-group differences to reflect the practical significance of the effects. In addition to traditional significance testing, Bayesian factor analysis (Bayes Factor Analysis) will be conducted, and BF₁₀ values will be reported to provide relative evidence strength between the null and alternative hypotheses, enhancing the multidimensional reliability of the interpretations.

This study is designed as a closed golf summer training camp, and all experimental measurements will be conducted within a unified time window. This centrally managed experimental environment helps to minimize the risk of dropouts or missing data due to personal factors (such as going out, absences), but the risk of missing data in repeated measures design still needs to be considered. Missing data will be handled using mixed-effects models combined with maximum likelihood estimation (ML) to retain all available data and obtain robust and unbiased effect estimates. When the proportion of missing data is high (such as more than 5%), multiple imputation will be adopted, and sensitivity analyses will be conducted to explore the impact of the missing data mechanism on study conclusions, thereby enhancing the credibility of the inferences.

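### The effect size for music versus no music is, on the natural reading, reported only when a test is significant, although the same section promises effect sizes for all analyses

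*Protocol article*

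**What the plan says.** Four statements in the Statistical analysis section of the protocol article bear on which results receive an effect size.

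- The opening sentence covers all tests, "with effect sizes measured using partial eta squared (η²p"). Cohen's d is not mentioned there.
- A later paragraph begins without any condition: "All statistical analyses will report effect size indicators".
- The sentence straight after it is conditional: "For significant results, partial eta squared (η²p) will be reported as the effect size for ANOVA, and Cohen’s d will be calculated for between-group differences".
- The route to any group comparison is conditional too: "If the interaction effect is significant, simple effects analysis will be conducted". That step contains the between-group differences at each time point, and "all post hoc group comparisons will apply Bonferroni correction".

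The section also promises Bayes factors (BF₁₀), with no condition on significance.

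**The concern.** The Introduction asks whether music mitigates the effect of mental fatigue on golf skill. The contrast that answers this is MF-Mu minus MF-nMu. Cohen's d is the only effect size the plan names for a difference between two groups. The other reported quantities do not replace it. Partial eta squared for the three-group interaction has 2 degrees of freedom and mixes the fatigue effect with the music effect. BF₁₀ measures relative evidence and gives no magnitude.

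An estimate shown only after a significant test is, on average, too far from zero. When it is withheld, the reader cannot separate a small effect from an imprecise one. This matters because the plan uses these effect sizes to judge practical significance, and the Discussion expects the results to guide golfers and coaches.

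**Working it through.** **1. The text.** Two neighbouring sentences conflict: one covers all analyses, the other significant results. By its grammar, the opening condition of the second governs both halves, partial eta squared and Cohen's d. Suppose instead that the Cohen's d half is unconditional. The between-group comparison is still planned only after a significant interaction, so a gate on significance remains under either reading.

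**2. The plan's own figure.** The inputs are in the Participants section: "Assuming a medium effect size f = 0.25 (Cohen’s standard), α = 0.05, power = 0.95, three groups, two measurement time points". The correlation ρ between the two times is given there as 0.5. For the repeated-measures within–between interaction:

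- λ = f² × N × m / (1 − ρ) = 0.0625 × 66 × 2 / 0.5 = 16.5
- degrees of freedom: (3 − 1)(2 − 1) = 2 and (66 − 3)(2 − 1) = 63
- power = 0.9535 at N = 66 and 0.9436 at N = 63

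So 66 (22 per group) is the smallest equal-group size for power 0.95, and the stated figure is reproduced.

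**3. What f = 0.25 means for the music contrast.** The protocol gives no expected music effect, so its pattern is an assumption. With SD 1 at both times and ρ = 0.5, the change score has variance 2(1 − 0.5) = 1, and λ = 22 × Σ(group mean change − overall mean change)². Setting λ = 16.5 gives a sum of 0.75. CON is taken as unchanged, and D is the fall in MF-nMu.

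- Music fully restores performance (changes 0, −D, 0): the sum is 2D²/3, so D = √1.125 = 1.06 and the true d is 1.06.
- Music half restores it (changes −D/2, −D, 0): the sum is D²/2, so D = √1.5 = 1.22 and the true d is 0.61.

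Two smaller scenarios were added. Falls of 0.8 SD (MF-nMu) and 0.3 SD (MF-Mu) give a true d of 0.5 and λ ≈ 7.2. Falls of 0.5 and 0.25 SD give a true d of 0.25 and λ = 2.75.

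**4. Simulation.** 40,000 trials were run per scenario with 22 per group. d is the post-test difference in means divided by the pooled SD. Gate A requires interaction p < 0.05. Gate B also requires the post-test MF-Mu versus MF-nMu comparison to have p < 0.05/3; three comparisons is an assumption that follows from three groups.

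| True d | λ | Mean d, always reported | Gate A: d missing | Gate A: mean d | Gate B: d missing | Gate B: mean d |
|---|---|---|---|---|---|---|
| 1.06 (full restoration) | 16.5 | 1.08 | about 5% | 1.09 | about 18% | 1.17 |
| 0.61 (half restoration) | 16.5 | 0.63 | about 5% | 0.63 | about 66% | 0.96 |
| 0.50 (falls 0.8 and 0.3) | 7.2 | 0.51 | 35% | 0.56 | about 82% | 0.94 |
| 0.25 (falls 0.5 and 0.25) | 2.75 | 0.25 | 71–72% | 0.34 | 97% | 0.89 |

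Repeat runs, and the choice of error term for the pairwise test, move these figures by about one percentage point or 0.01 to 0.02 in d. The slight excess in the always-reported column is the ordinary small-sample bias of Cohen's d.

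**The case against.** The strongest reply is that two general statements promise effect sizes without condition, so the disputed sentence may only be matching each index to its analysis. Testing simple effects after a significant interaction is also a usual ANOVA sequence and fits the stated core hypothesis. The sequence is indeed a legitimate way to order tests. But the literal wording restricts both indices, and the harmonised reading still leaves the group comparison behind the interaction test.

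Three stronger readings are tempting, and the document does not support them.

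- A reader might infer that the music effect will always be either missing or inflated. At the planned effect, with the interaction as the only gate, d is missing in about 5% of trials and its mean barely changes. The large inflation needs the pairwise test to define significance, which the plan does not say.
- A reader might infer that a non-significant trial would yield no information on music at all. Nothing says that means and SDs will be withheld, and with those and n a reader could calculate d. What is conditional is the planned reporting of the contrast.
- A reader might infer that the Participants section withholds effect sizes and Bayes factors unless recruitment falls short, because there "the study will report effect sizes and Bayes factors to supplement the interpretation of statistical significance". It says they will help interpretation in that case, not that they are omitted otherwise, and BF₁₀ is promised regardless.

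**Conclusion.** The point stands as a contradiction in the stated reporting rule, with a consequence for the one effect size that isolates music. The size of that consequence is not a single number. At the planning effect it is negligible if only the interaction gates reporting. It is material if the pairwise test does as well, most clearly when music restores half of the loss (mean reported d 0.96 / always-reported mean 0.63 = 1.5 times). If the true d is nearer 0.5, the interaction gate alone already removes the comparison in about a third of trials and raises mean d from 0.51 to 0.56.

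These results rest on assumed true effects, an unchanged control group and normal outcomes. The sample size and correlation are the plan's. The primary interaction test, its alpha and its power are unaffected.

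**What to change.** In the Statistical analysis section, delete the opening phrase that limits the effect-size sentence to significant results, and state one rule. For example:

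*Whatever the p-value or the interaction result, partial eta squared will be reported for every ANOVA effect. The pairwise group differences, above all MF-Mu minus MF-nMu, will be reported with 95% confidence intervals and Cohen's d, at least for the primary accuracy outcome.*

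Hypothesis tests of these differences may stay conditional on the interaction. The Participants section needs no change on this point. The cost is a few more table rows. No further data or tests are needed, and the type I error of the planned tests does not change. The Status and timeline section says that recruitment had not begun, so on that status the rule can still be set before any data exist.

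### Maximum likelihood is named for the missing-data mixed model; at low missingness it puts the time × group test at about 5.6–5.7% instead of 5% (minor), and REML removes this

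*Protocol article*

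**What the plan says.** All references are to the protocol article.

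- **Main analysis (Statistical analysis).** A 2 × 3 mixed-design ANOVA, time by group. On the test of interest the section states: "The core hypothesis of the study is the time × group interaction effect". Main effects are secondary.
- **Error rate (Statistical analysis).** "All statistical tests will be conducted at a significance level of α = 0.05". Bonferroni and Holm-Bonferroni corrections are added for multiple comparisons.
- **Missing data (Statistical analysis).** "Missing data will be handled using mixed-effects models combined with maximum likelihood estimation (ML) to retain all available data". The article expects this to give effect estimates that are robust and free of bias. The next sentence moves to multiple imputation, with sensitivity analyses, when missingness is high, and offers more than 5% as the example.
- **Sample size (Participants).** "the study requires at least 66 participants (22 per group) to ensure sufficient power for detecting the interaction effect". The recruitment target is then raised to 76 for an assumed 15% dropout.

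The article does not name the test statistic or the degrees of freedom for the mixed model.

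**The concern.** ML and REML use the same observations and rest on the same missing-at-random assumption. They differ in how they estimate the variance. ML makes no allowance for the fixed effects that were estimated, so its variance is too small in a modest sample. REML makes that allowance and, with complete data and two time points, agrees with the planned ANOVA.

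The article takes care over Type I error, yet for incomplete data it names the estimator whose tests run slightly above the nominal level. At stake are the size of the core interaction test and the width of the intervals whenever the ML model is the one reported.

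**Working it through.** **Inputs.** From Participants: "Assuming a medium effect size f = 0.25", and "α = 0.05, power = 0.95, three groups, two measurement time points, and an intra-class correlation (ICC) of 0.5"; N = 66 evaluable and 76 recruited. From Statistical analysis: α = 0.05, time × group as the core test, ML for missing data.

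**1. The plan's own sample size.** Noncentral F with λ = f²·N·m/(1 − ρ) and degrees of freedom 2 and N − 3. At N = 66, λ = 0.0625 × 66 × 2/0.5 = 16.5 and power is 0.953. At N = 63 power is 0.944. So 66 is reproduced. The 76 matches 66 × 1.15 = 75.9 (66/0.85 would give 78; this does not affect the present point).

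**2. What ML does to the test.** With two time points, the interaction test equals a one-way ANOVA on change scores in three groups.

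- ANOVA or REML variance: RSS/(N − 3).
- ML variance: RSS/N.
- F under ML is therefore too large by N/(N − 3): 66/63 = 1.048 at N = 66 and 76/73 = 1.041 at N = 76.
- Standard errors shrink by √(63/66) = 0.977 (2.3% too small) and √(73/76) = 0.980 (2.0% too small).

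**3. True size.** Size = P[F(2, N − 3) > c·(N − 3)/N], where c is the critical value used. At N = 66 with N − 3 degrees of freedom, c = 3.143 and c × 63/66 = 3.000. With 2 numerator degrees of freedom the tail has a closed form: (1 + 2 × 3.000/63)^(−31.5) = 0.0570.

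| Reference for c | ML, N = 66 | ML, N = 76 |
|---|---|---|
| F, N − 3 df | 5.70% | 5.60% |
| F, N df | 5.73% | 5.63% |
| Chi-square (not stated in the article) | 6.5% | 6.3% |

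REML with N − 3 degrees of freedom gives 5.0% at both sizes.

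**4. Simulation with missing scores.** The formula is exact for complete data, so it was checked with a random-intercept model, correlation 0.5, post-test scores missing completely at random, an F reference based on complete golfers minus 3, and 40,000 replicates per row (Monte Carlo standard error about 0.11 points).

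| N | Missing post scores | ML | REML | Complete-case ANOVA |
|---|---|---|---|---|
| 66 | 0 | 5.80% | 5.14% | 5.14% |
| 66 | 1 | 5.79% | 5.10% | 5.12% |
| 66 | 3 | 5.84% | 5.20% | 5.10% |
| 76 | 0 | 5.57% | 4.91% | 4.91% |
| 76 | 1 | 5.56% | 4.99% | 4.96% |
| 76 | 3 | 5.58% | 4.97% | 4.97% |

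The gap between ML and REML is about 0.6–0.7 points in every row, including those with nothing missing. It comes from the variance divisor.

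**5. Where the ML path applies.** One missing score is 1/132 = 0.8% of scores at N = 66, or 1/152 = 0.7% at N = 76, well under 5%. The plan's own 15% dropout at N = 76 would be about 11.4 golfers. If each missed the post-test, 11.4/152 = 7.5% of scores, or 15% of golfers, would be incomplete. Either count exceeds 5% and goes to imputation.

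**The case against.** **The scope is limited.** A reader might infer that the core test is inflated whenever any score is missing. The article does not support that. Heavier missingness goes to multiple imputation, and the plan's own dropout assumption falls there. How the imputed data are then modelled is not stated. This stands, and it confines the point to low missingness.

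**No trigger is stated.** It is also tempting to say that one missing score moves the test from 5% to 5.7%. The article gives no such switching rule and does not say that the ANOVA is then abandoned. The missing score is not the cause either, since ML gives the same excess with complete data.

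**The claim about bias is not false.** The article claims freedom from bias for effect estimates, and ML does not bias the fixed effects here. The fault lies in standard errors, tests and intervals.

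**ML is not simply a worse choice than the ANOVA.** A repeated-measures ANOVA drops golfers with a missing score; the likelihood model keeps them and is valid under missing at random. The simulation removed scores completely at random, so it compares size only. This stands as a defence of the mixed model, but not of ML, because REML has the same advantage.

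**Detail may sit in the analysis plan.** Degrees-of-freedom methods and reference distributions are commonly left to it, and their absence is not criticised. The estimator, however, is a stated choice.

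**Conclusion.** The point holds in a narrow form and is minor. Where missingness is low enough for the ML mixed model to be the reported analysis, the time × group test has a true size of about 5.7% at N = 66, or 5.6% at N = 76, against 5%, and standard errors are about 2% too small.

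This assumes an F reference with about N − 3 or N denominator degrees of freedom. The 6.3–6.5% range needs a chi-square reference that the article does not state. It also assumes that the 5% example works as the boundary with imputation; whether it counts scores or golfers is not said.

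A reader might extend the finding to the Bonferroni comparisons. Algebra puts a pairwise test at nominal 0.0167 at about 0.019. The only simulation of it (6,000 runs) gave 0.0175 with a standard error of about 0.0017, which cannot be told apart from nominal. No separate claim is made there.

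**What to change.** In the missing-data sentence of Statistical analysis, replace maximum likelihood (ML) by restricted maximum likelihood (REML), with small-sample degrees of freedom such as Satterthwaite, for all reported tests and intervals. ML can be kept for likelihood-ratio comparisons of models that differ in their fixed effects.

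The cost is a phrase and one software option. No data are lost, the missing-at-random basis is unchanged, and p-values become slightly larger. The article reports that neither recruitment nor data collection had begun, so on that status the change could be made before any data are seen.
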